#### Criteria for discontinuing or modifying allocated interventions {11b}

Based on the known potential risks associated with short-term amiodarone administration, the following are indications of discontinuation: allergic reaction; hypotension (systolic BP<90); bradycardia (heart rate <50bpm); AV blockade (PR interval prolonged on electrocardiogram >0.20 seconds); ARDS (i.e., if unexplained progressive hypoxemia (berlin definition) with PF ratio <200); and QT prolongation (i.e., heart rate-corrected QT interval prolonged to >500ms) [18–22].

Given that amiodarone is also a treatment option for POAF, we will reveal the allocation group of randomized patients who develop POAF (defined as an irregularly irregular atrial rhythm without clear P waves, recorded on a standard 12-lead electrocardiogram (ECG) that occurred in the immediate 30-day postoperative period [3]) to allow clinicians to provide appropriate treatment doses of amiodarone.

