#### Adverse event reporting and harms {22}

Amiodarone’s pharmacokinetic properties (namely its long half-life and prolonged washout period) as well the severe nature of some of its side effects make close monitoring essential among patients treated with this drug. Fortunately, many of the known adverse effects are secondary to tissue accumulation of amiodarone and are not seen with short-term therapy.

Below is a summary of how adverse events will be managed:
*Allergic reaction*: If there is appearance of an allergic reaction, the study drug will be stopped immediately. Symptoms of the allergic reaction will be managed with supportive measures including antihistamines and intra-muscular epinephrine, as appropriate.*Hypotension*: If hypotension occurs with reasonable clinical suspicion that it is secondary to the intervention, treatment will be withdrawn. Hypotension will be treated with fluid resuscitation and vasopressor therapy, as indicated.*Bradycardia/AV blockade*: If bradycardia or AV blockade occurs with reasonable clinical suspicion that it is secondary to the intervention, treatment will be withdrawn. Severe bradycardia may require pharmacological treatment with atropine, dopamine, or epinephrine, or may require transcutaneous pacing. Our cardiology service will be consulted to assist with management as necessary.*ARDS*: If ARDS occurs (as defined under the Berlin definition), treatment will be withdrawn. ARDS will be managed according to standard of care with supportive treatments. Our respirology and/or intensive care teams will be consulted as needed to assist with management.*QT prolongation:* If QTc interval is prolonged with reasonable clinical suspicion that it is secondary to the intervention, treatment will be withdrawn. Any electrolyte abnormalities that would predispose the patient to cardiac arrhythmia will be corrected. Development of any ventricular arrhythmias will be managed in accordance with standard of care. Our cardiology service will be consulted to assist with management as necessary.

In the event of development of a significant adverse event, clinical follow-up will be arranged as necessary with our cardiology service.

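### The two statements of the study-drug stopping rule disagree on ARDS and leave attribution open, and the PR trigger, read literally, can be met before the first dose

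*Protocol article*

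**What the plan says.** The protocol article states the rule for stopping study drug in two sections.

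- **Criteria for discontinuing {11b}.** After a reference to the known risks of short-term amiodarone, it says that "the following are indications of discontinuation: allergic reaction; hypotension (systolic BP<90); bradycardia (heart rate <50bpm); AV blockade (PR interval prolonged on electrocardiogram >0.20 seconds". The list continues with "ARDS (i.e., if unexplained progressive hypoxemia (berlin definition) with PF ratio <200" and "QT prolongation (i.e., heart rate-corrected QT interval prolonged to >500ms". No item carries a condition that the drug be the suspected cause.
- **Adverse event reporting and harms {22}.** This part introduces itself with "Below is a summary of how adverse events will be managed". On individual events it says "If hypotension occurs with reasonable clinical suspicion that it is secondary to the intervention, treatment will be withdrawn", "If bradycardia or AV blockade occurs with reasonable clinical suspicion that it is secondary to the intervention, treatment will be withdrawn" and "If QTc interval is prolonged with reasonable clinical suspicion that it is secondary to the intervention, treatment will be withdrawn". ARDS is worded differently: "If ARDS occurs (as defined under the Berlin definition), treatment will be withdrawn". None of the numeric limits of {11b} is repeated.

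Neither section refers to the other or says which governs.

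On entry, the eligibility section {10} excludes second- or third-degree heart block without a pacemaker and a QTc above 450 ms. It sets no limit on the PR interval.

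**The concern.** This is a safety rule, and bedside staff could read it in either place. Two clinicians facing the same event could act differently and each point to the protocol.

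ARDS matters most. The background section names it as a concern with high-dose amiodarone in pneumonectomy patients, and the trial enrolls pneumonectomy patients. Hypotension is the likely everyday case: the infusion starts at anesthesia induction and runs for 24 hours, so a systolic pressure below 90 put down to anesthesia falls inside the dosing window.

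The outcomes section {12} also counts divergences from the approved protocol and monitors adherence to the safety protocols. Neither can be recorded consistently while the rule reads two ways. The statistical methods section plans to carry these data into a full-scale trial, so the ambiguity could go with them.

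**Working it through.** No figure in the plan is at issue, so the check is a side-by-side reading.

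**Step 1. Compare the two sections event by event.**

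| Event | {11b} | {22} | Same rule? |
|---|---|---|---|
| Allergic reaction | listed | stop at once | yes |
| Hypotension | SBP <90, cause not mentioned | if drug suspected, no number | open on attribution |
| Bradycardia | HR <50, cause not mentioned | if drug suspected, no number | open on attribution |
| AV block | PR >0.20 s, cause not mentioned | if drug suspected, no number | open on attribution |
| QT prolongation | QTc >500 ms, cause not mentioned | if drug suspected, no number | open on attribution |
| ARDS | unexplained and progressive, PF <200 | any Berlin-defined ARDS | no |

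Of six events, one agrees, four share one open question (attribution), and one has two different definitions: 1 + 4 + 1 = 6.

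**Step 2. Test whether one principle reconciles them.** Suppose {11b} supplies the thresholds and {22} adds a judgment on cause. For the four attribution events this works: {22} is then the narrower text. For ARDS it fails, because the restriction on cause sits in {11b} and is absent from {22}. Take an ARDS with an identified cause. Under {22} treatment is withdrawn. Under {11b} the hypoxemia is not unexplained, so the event is not a listed indication. This follows from the wording alone and needs no Berlin cut-off.

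**Step 3. Take an unattributed event.** A systolic pressure below 90 ascribed to anesthesia is an indication under {11b}. The condition given in {22} is not met. Since {22} says *if* and not *only if*, stopping breaches neither section. What the text does not settle is whether continuing is allowed.

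**Step 4. Compare entry limits with stopping limits for the two ECG intervals.**

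- QTc: the entry limit is 450 ms and the stop is above 500 ms. The margin is 500 − 450 = 50 ms, so a patient within the entry limit does not start above the stop.
- PR: there is no entry limit and the stop is above 0.20 s (200 ms). No margin is guaranteed. The only conduction blocks excluded by degree are second and third, so a patient with a longer PR and no such block can be eligible and meet the literal criterion before dosing.

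**The case against.** The strongest reply is that the sections are meant to be read together. An indication is a ground for stopping, not an order to stop at each reading; {22} is a summary that adds clinical judgment, which suits a pragmatic trial with an independent DSMB. For the four attribution events this is a fair reading, and it reduces that part to a gap in the text. It does not rescue ARDS, for the reason in Step 2. It is also true that withdrawing for an explained ARDS violates nothing in {11b}. The practical risk is that someone working from {11b} alone continues the drug when {22} says it is withdrawn.

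On PR, the word *prolonged*, in a list of drug risks, may well mean a change on treatment, and a PR unchanged since before dosing gives little reason to suspect the drug. That is probably the intention. The text nevertheless gives only an absolute value, and the {22} attribution clause helps only if attribution is required, which is the unsettled question. The exclusion for contraindications to amiodarone might remove some of these patients, but the article does not say what it covers.

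A reader might go further in four ways that the document does not support:

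- That the two sections directly contradict each other on hypotension, bradycardia, AV block and QT. They do not, because {22} never says *only if*.
- That the PF ratio limits differ by a known amount. Both sections name Berlin, but the article does not give its cut-offs, so the gap cannot be sized.
- That the heart-rate trigger has the same baseline problem because beta-blocker users are eligible. It is possible, but the undefined contraindication exclusion makes it less firm.
- That the 90% adherence criterion is endangered. That would need a baseline frequency of long PR and a rule that counts safety stops as non-adherence; the article gives neither.

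**Conclusion.** The point holds in three parts of unequal weight. The ARDS rules conflict as written: an explained ARDS is a ground for withdrawal in {22} and not in {11b}. The attribution question for four events is left open rather than contradictory. The PR trigger, read literally, can be satisfied before the first dose; this rests on taking the absolute value at face value.

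How many patients would be affected, and any effect on exposure or deviation counts, cannot be derived from the document. No endpoint, sample size or test changes. Severity is minor to moderate: a small inconsistency, worth correcting because it sits in a safety rule.

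**What to change.** Three wording changes:

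1. **ARDS.** In {11b}, replace the criterion with the {22} rule: withdraw study drug for any Berlin-defined ARDS, whether or not a cause is identified.
2. **Attribution.** State once, in the same words in both sections, that the {11b} thresholds are the triggers, and say whether suspected drug causation is also required. Which way to decide is a clinical choice for the investigators and the DSMB.
3. **AV block.** Define the criterion as new prolongation of the PR interval beyond 0.20 s on treatment, relative to the preoperative ECG.

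The cost is a few lines of text and the usual REB handling of an amendment. An ECG before surgery is already needed to apply the QTc exclusion. Sample size, randomization and outcomes are unchanged.

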#### POAF prophylaxis and safety

Of the agents that have been used for prophylaxis, metoprolol and amiodarone are most effective at preventing POAF [2, 6]. Unfortunately, the use of metoprolol for prophylaxis in a generalized manner after non-cardiac surgery is associated with increased risk of stroke and death [7]. Amiodarone, a Class III anti-arrhythmic, has been extensively studied as a prophylactic agent for POAF, effectively reducing the rate of POAF by as much as 31% after thoracic surgery, with a total relative risk (RR) of 0.22 (*P* = 0.001; 95% CI, 0.09–0.54) and a NNT of 5.1 [6]. However, the safety of prophylactic amiodarone has also been controversial; high dosing regimens have been associated with hypotension, bradycardia, QT prolongation, and in patients undergoing pneumonectomy, adult respiratory distress syndrome (ARDS), in addition to more common effects of tremor, nausea, and constipation [8]. Several recent trials have suggested administration of low dose prophylactic amiodarone to patients undergoing non-cardiac thoracic surgery to be safe [9–13]. Given its effectiveness, but concern regarding toxicity, the Society of Thoracic Surgeons (STS) most recent 2011 guidelines only recommend amiodarone prophylaxis for patients undergoing esophagectomy, and pulmonary resection, excluding pneumonectomy, until additional data addressing its potential for pulmonary toxicity is available (class III recommendation) [14]. The American Association of Thoracic Surgeons 2014 guidelines recommends surgeons consider prophylactic amiodarone for the prevention of POAF for intermediate and high-risk patients undergoing pulmonary resection (class IIa recommendation) and for all patients undergoing esophagectomy (class IIb recommendation) to minimize potential side effects of amiodarone [1]. However, until recently, there have been no validated tools to identify patients at elevated risk of POAF.

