### Trial design {8}

The PREP-AF feasibility trial is a pragmatic single-center, parallel group, double-blinded, randomized controlled feasibility study.

Individuals will first be assessed for their risk of POAF based on their POAF prediction score (Table 1) and planned procedure.

**Table 1 Tab1:** POAF prediction score [15, 17]

Criteria	Points
Male gender	1
HR^a^ >72 bpm	1
Age 55–74 years	3
Age >75 years	4
Total	/6

^a^Heart rate (HR)

Individuals will be considered “high-risk” of POAF by meeting both of the following criteria: (1) POAF prediction score greater than or equal to 4 (Table 1) and (2) undergoing lobectomy, extended lobectomy, pneumonectomy, or esophagectomy.

High-risk individuals will be randomized 1:1 to intervention or control group.

Individuals will be considered “low-risk” of POAF by one the following criteria: (1) POAF prediction score less than 4 (Table 1) or (2) undergoing gastrectomy or sublobar resection.

Low-risk individuals will receive standard care with monitoring for clinical outcomes and adverse events.

Patients using beta-blockers at the time of enrollment will be eligible to participate in the trial. Given that beta-blocker use is protective against development of POAF, we will stratify these patients at the time of randomization to ensure the proportion of beta blocker usage is equal between intervention groups.

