## Methods: participants, interventions, and outcomes

### Study setting {9}

This study will be conducted with the Division of Thoracic Surgery at The Ottawa Hospital, an academic teaching center in Ottawa, Ontario, Canada. At our center, approximately 200 patients undergo major thoracic surgery annually. Of which, 52% undergo a lobectomy, 25% a sublobar resection, 5% a pneumonectomy, and 11% an esophagectomy.

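### The two ARDS stop rules differ: item 11b covers only unexplained hypoxemia, while item 22 withdraws study drug for any Berlin-defined ARDS

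*Protocol article*

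**What the plan says.** Two sections of the protocol article say when study drug must stop for ARDS.

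- **Criteria for discontinuing or modifying allocated interventions {11b}** lists the indications for stopping. The ARDS entry is "ARDS (i.e., if unexplained progressive hypoxemia (berlin definition) with PF ratio <200".
- **Adverse event reporting and harms {22}** sets out the management of each event. For ARDS it says: "If ARDS occurs (as defined under the Berlin definition), treatment will be withdrawn".

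Three other events in {22} carry a condition on cause that ARDS does not:

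- Hypotension: "If hypotension occurs with reasonable clinical suspicion that it is secondary to the intervention, treatment will be withdrawn".
- Bradycardia or AV blockade: "If bradycardia or AV blockade occurs with reasonable clinical suspicion that it is secondary to the intervention, treatment will be withdrawn".
- QT prolongation: "If QTc interval is prolonged with reasonable clinical suspicion that it is secondary to the intervention, treatment will be withdrawn".

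Neither section refers to the other, and nothing in the article says which one governs.

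**The concern.** Both sections give a rule for stopping the same drug for the same event, and they treat its cause differently. In {11b}, the abbreviation *i.e.* makes what follows read as the definition of the trigger, and that definition contains the word *unexplained*. In {22}, ARDS alone is enough.

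Two things are at stake.

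- **Safety.** A clinician working only from the section on stopping criteria could judge that ARDS with an identified cause is not an indication to stop, and could keep the patient on blinded, possibly active amiodarone. The surgical care team is blinded (Who will be blinded {17a}), so it would have to judge whether the hypoxemia is explained without knowing the allocation. Unblinding is available {17b}, but neither stop rule depends on it. ARDS is also a harm that the background names for high dosing regimens: "in patients undergoing pneumonectomy, adult respiratory distress syndrome (ARDS". Pneumonectomy is among the qualifying procedures: "undergoing lobectomy, extended lobectomy, pneumonectomy, or esophagectomy".
- **Recording of deviations.** Outcomes {12} makes the monitoring of protocol deviations one of the feasibility measures. Continuing drug in such a patient could be recorded as following the protocol under {11b} or as departing from it under {22}.

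**Working it through.** No arithmetic applies, because the point rests on wording. The two lists, side by side:

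| Event | {11b}: condition on cause? | {22}: condition on cause? |
|---|---|---|
| Allergic reaction | None | None |
| Hypotension | None (systolic BP below 90) | Yes, suspected relation to the intervention |
| Bradycardia / AV blockade | None (heart rate below 50; PR above 0.20 s) | Yes, suspected relation |
| QT prolongation | None (corrected QT above 500 ms) | Yes, suspected relation |
| ARDS | Yes, hypoxemia must be unexplained; PF below 200 | None; Berlin definition; no separate PF figure |

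1. In {11b}, ARDS is the only event with a qualifier on cause. In {22}, ARDS and allergic reaction are the only events without one. On this question the two lists run in opposite directions.

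2. Apply both rules to three kinds of patient still on study drug:
   - *Berlin-defined ARDS, no cause found, PF below 200.* Both sections stop the drug.
   - *Berlin-defined ARDS, PF below 200, attributed to a known cause such as postoperative pneumonia.* The {11b} entry, read literally, is not met because the hypoxemia is explained. The {22} rule is met and the drug is withdrawn.
   - *PF of 200 or more.* The {11b} entry is not met. Whether {22} is met depends on the PF ceiling in the Berlin definition, which the article does not reproduce. This case is left open and no conflict is claimed on it.

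3. Check whether the second case forces opposite actions. {11b} lists indications; it does not say they are the only ones and does not tell staff to continue otherwise. {22} is mandatory. Someone applying both would withdraw the drug. The inconsistency therefore takes effect only when {11b} is read alone, or when a deviation is judged against one section rather than the other.

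4. Look for a reconciling statement. None was found in the sections on intervention, concomitant care, blinding, unblinding, data monitoring or adverse events.

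5. Consider size. The article gives no ARDS incidence, so affected patients cannot be counted. The exposure is short: study drug runs from the day of surgery to postoperative day 5 or discharge, whichever comes first (Intervention description {11a}).

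**The case against.** The strongest reply is that both sections invoke the same standard. In {11b} the Berlin label sits directly after the words about progressive hypoxemia, so *unexplained* may be a loose paraphrase of the Berlin definition and not an added test of cause. The definition is not reproduced, so the article cannot settle this. The point reduces the weight of the finding but does not remove it. If the word adds nothing, it is redundant in a safety rule and can mislead, and the two printed rules still differ.

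The second reply is that the rules are compatible, because following both leads to withdrawal. That is correct, and it rules out the stronger reading that the protocol orders opposite actions for the same patient. What remains is that the section whose title concerns discontinuation prints the narrower wording and does not point to the wider one.

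The third reply is that this is a condensed article, that {22} calls its list a summary, and that ward staff may work from fuller documents. This also lowers the weight. But the finding is not about an omission: both rules are printed in the current text and they do not match.

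The fourth reply is that the text could be harmonised the other way, by adding the qualifier to {22}. It could. The choice to delete it is a judgement in favour of safety. It is supported by the fact that {22} attaches a suspicion condition to three other events and leaves it off ARDS.

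**Conclusion.** The point holds as a minor wording conflict. For ARDS attributed to a known cause, {22} requires withdrawal and {11b}, read alone, gives no trigger. Continuing drug in such a patient could be classed either way in deviation monitoring. The conclusion rests on reading *unexplained* literally and on {22} meaning what it says when it sets no cause condition.

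A reader might infer more, and the document does not support it:

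- **That patients will be harmed.** The background ties ARDS to high dosing regimens, and {11a} considers the trial's own regimens safe. This is a risk created by wording, not a shown excess of harm.
- **That the number of pneumonectomy patients measures the problem.** The procedure mix in Study setting {9} describes who undergoes surgery, not who develops ARDS with an attributed cause while on drug.
- **That the ≥90% adherence criterion would be misjudged.** Without an ARDS incidence, no such effect can be shown.
- **That the PF limits conflict.** The Berlin ceiling is not stated in the article.

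**What to change.** Delete *unexplained* from the ARDS entry in {11b}, and use one rule in both {11b} and {22}: study drug is withdrawn for Berlin-defined ARDS regardless of presumed cause. State one PF limit, whichever the sponsor intends, in both places.

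While the text is open, the sponsor could also settle the reverse mismatch for hypotension, bradycardia or AV blockade, and QT prolongation, where {11b} sets no cause condition and {22} does.

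The cost is a short amendment, reviewed by the Research Ethics Board as the amendments section {25} provides. It needs no extra data, procedures or patients. The downside is possibly a few more discontinuations among patients whose ARDS has another explanation.

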#### Strategies to improve adherence to interventions {11c}

No additional strategies will take place to improve adherence to this trial, in keeping with the pragmatic design of this study.

#### Relevant concomitant care permitted or prohibited during the trial {11d}

Both groups will receive standard postoperative care in accordance to the existing pathways for postoperative thoracic surgical care at our institution. This includes routine postoperative electrolyte monitoring and replacement (during the inpatient stay for the first 3 days postoperatively). All patients will receive routine continuous heart rate monitoring for 48–72 h after surgery, discontinued at clinical discretion. Management of POAF will be guided by the published algorithm developed at our institution with the final decisions regarding rate control therapy and anticoagulation left to the discretion of the treatment team and with involvement of the cardiology team where appropriate [23].

